# A best practice fall prevention exercise program to improve balance, strength / power, and psychosocial health in older adults: study protocol for a randomized controlled trial

**DOI:** 10.1186/1471-2318-13-105

**Published:** 2013-10-09

**Keywords:** Seniors, Fall risk assessment, Resistance training, Postural stability

## Abstract

**Background:**

With increasing age neuromuscular deficits (e.g., sarcopenia) may result in impaired physical performance and an increased risk for falls. Prominent intrinsic fall-risk factors are age-related decreases in balance and strength / power performance as well as cognitive decline. Additional studies are needed to develop specifically tailored exercise programs for older adults that can easily be implemented into clinical practice. Thus, the objective of the present trial is to assess the effects of a fall prevention program that was developed by an interdisciplinary expert panel on measures of balance, strength / power, body composition, cognition, psychosocial well-being, and falls self-efficacy in healthy older adults. Additionally, the time-related effects of detraining are tested.

**Methods/Design:**

Healthy old people (n = 54) between the age of 65 to 80 years will participate in this trial. The testing protocol comprises tests for the assessment of static / dynamic steady-state balance (i.e., Sharpened Romberg Test, instrumented gait analysis), proactive balance (i.e., Functional Reach Test; Timed Up and Go Test), reactive balance (i.e., perturbation test during bipedal stance; Push and Release Test), strength (i.e., hand grip strength test; Chair Stand Test), and power (i.e., Stair Climb Power Test; countermovement jump). Further, body composition will be analysed using a bioelectrical impedance analysis system. In addition, questionnaires for the assessment of psychosocial (i.e., World Health Organisation Quality of Life Assessment-Bref), cognitive (i.e., Mini Mental State Examination), and fall risk determinants (i.e., Fall Efficacy Scale – International) will be included in the study protocol. Participants will be randomized into two intervention groups or the control / waiting group. After baseline measures, participants in the intervention groups will conduct a 12-week balance and strength / power exercise intervention 3 times per week, with each training session lasting 30 min. (actual training time). One intervention group will complete an extensive supervised training program, while the other intervention group will complete a short version ('3 times 3’) that is home-based and controlled by weekly phone calls. Post-tests will be conducted right after the intervention period. Additionally, detraining effects will be measured 12 weeks after program cessation. The control group / waiting group will not participate in any specific intervention during the experimental period, but will receive the extensive supervised program after the experimental period.

**Discussion:**

It is expected that particularly the supervised combination of balance and strength / power training will improve performance in variables of balance, strength / power, body composition, cognitive function, psychosocial well-being, and falls self-efficacy of older adults. In addition, information regarding fall risk assessment, dose–response-relations, detraining effects, and supervision of training will be provided. Further, training-induced health-relevant changes, such as improved performance in activities of daily living, cognitive function, and quality of life, as well as a reduced risk for falls may help to lower costs in the health care system. Finally, practitioners, therapists, and instructors will be provided with a scientifically evaluated feasible, safe, and easy-to-administer exercise program for fall prevention.

**Trial registration:**

ClinicalTrials.gov Identifier: NCT01906034

## Background

Worldwide, the number of people over 60 years is growing faster than any other age group and expected to grow from 688 million in 2006 to almost 2 billion by 2050 [1]. The main reasons for this substantial demographic change are higher life expectancy and declining birth rates [2]. This future increase in the proportion of older adults is important from a public health perspective [3]. Aging is generally associated with progressive decline in physical and psychological health [4,5], increased risk of disability and dependency [4], as well as an increase in the number of comorbidities [6]. This decrease in health status is mainly responsible for one of the most common and serious public health problems, namely falls. Over 33% of community-dwelling people aged over 65 years fall at least once a year, and of those 50% will have recurrent falls [7,8]. With increasing age, the rate of falls can increase up to 60% [7,9]. Older adults suffering from cognitive decline may fall twice as often compared to their healthy counterparts [10], while institutionalized older adults in nursing homes or old people’s homes fall even more often [11].

Despite frequent falling in older adults, only one in five falls requires medical attention while less than 10% lead to a fracture [12]. However, in terms of morbidity and mortality, injurious falls have serious consequences of which the hip fracture is the most feared one [13]. Hip fractures often affect functionality and autonomy of older adults [14], and are associated with an overall mortality of 22% to 29% one year after injury [15]. In this context, 27% of older adults require a walking aid one year after a hip fracture surgery [16]. Despite rehabilitation, many individuals do not regain the level of functional performance they had before the fracture [14] which is why fall prevention is important.

Detection of fall risk factors is essential to implement effective and specifically tailored fall prevention strategies [17]. Some fall risk factors are irreversible while others are potentially modifiable with appropriate interventions [18,19]. Regularly conducted objective, reliable and valid fall risk assessment protocols can assist in identifying individuals at risk to make recommendations and optimize prevention strategies [20]. Three of the most common modifiable intrinsic (subject-related) fall risk factors are muscle weakness (relative risk ratio / odds ratio 4.4), balance deficits (relative risk ratio / odds ratio 2.9), and gait instabilities (relative risk ratio / odds ratio 2.9) [9,19,21]. These intrinsic risk factors may be modified by exercise referred to as structured, planned and repetitive physical activities in community-based organized exercise programs [22,23].

Balance is important for maintaining postural equilibrium and thus for the avoidance of falls. Aging may affect central nervous system (i.e., changes in brain volume) and neuromuscular system properties (i.e., loss of sensory and motor neurons) leading to deficits in balance and gait performance [24]. According to Shumway-Cook and Woollacott [25] balance can be subdivided into static / dynamic steady-state (i.e., maintaining a steady position in sitting, standing and walking), proactive (i.e., anticipation of a predicted disturbance), and reactive (i.e., compensation of a disturbance) balance [26,27]. Recently, Muehlbauer et al. [26] were able to show that there is no significant association between measures of steady-state, proactive, and reactive balance in healthy older adults. Thus, for testing and training purposes, balance tests and exercises should target all three domains separately and additionally include dual or multi tasks situations [26], given that multi-tasking is required for the performance of many activities of daily living (ADL, e.g., walking downstairs while talking on the phone) [28,29]. Furthermore, specific balance exercises may help to counteract balance deficits and gait instabilities by reducing the risk of falls in older adults [30-33].

Besides balance, muscle strength / power is required for the successful performance of ADL [26]. General causes of age-related skeletal muscle mass loss (i.e., sarcopenia) are manifold (e.g., cellular, neural, metabolic, hormonal contributors) [5,34,35]. For the diagnosis of age-related sarcopenia the European Working Group on Sarcopenia in Older People (EWGSOP) recommends using the criteria low muscle mass plus either low muscle strength or low physical performance measured by gait velocity (≤80 cm/s), grip strength and muscle mass [36]. Humans loose approximately 20% to 30% of their skeletal muscle mass between young adulthood and 80 years of age [37]. This loss in muscle fibre size and number predominantly occurs in type II muscle fibers which lead to a more rapid decline in muscle power compared to overall muscle strength [38]. This is detrimental because muscle power is an important prerequisite for quick postural reactions in response to external perturbations [39]. Older adults often use the hip or step strategy when balance is threatened [7,32]. A decrease in muscle power would delay such postural reactions to external perturbations [40,41], probably leading to a loss of balance [42] and ultimately resulting in a fall [7].

Based on a thorough fall-risk assessment, specifically tailored balance and resistance training programs can be developed which have the potential to improve important intrinsic fall-risk factors like deficits in muscle strength / power and balance performance [27]. For fall prevention, exercises for the promotion of static / dynamic steady-state, proactive and reactive balance should be trained complementarily [43]. Progression during training can be achieved by reducing the base of support (e.g., bipedal, step, tandem, monopedal stance) and by diminishing the sensory input (e.g., exercises with eyes opened / closed; exercises on stable / unstable surfaces) [21,44]. Additionally, resistance training with a focus on muscle strength / power for the lower extremities and the trunk muscles [45] seems essential for counteracting intrinsic fall risk factors (i.e., muscle weakness) in older adults.

During the past decades, many fall prevention interventions have proven a positive effect of exercise on intrinsic fall risk factors [12]. Despite substantial evidence, these programs have not been sufficiently implemented into clinical practice [46]. To reduce the burden of falls in older adults, easy-to-administer fall prevention programs need to be developed and implemented nationwide. However, lack of skilled people, inadequate communication between researchers, policy makers and clinicians, and health system barriers including inadequate financial resources hinder the implementation of new research evidence into practice [46,47]. Besides a lack of evidence about how fall prevention can be incorporated into community services [48], there is hardly any data available regarding dose–response relationships for optimal exercise for fall prevention. Hence, the Swiss Council for Accident Prevention (bfu) convened an international expert panel (n = 8) consisting of geriatricians, physiotherapists, and health, sports, exercise, accident and fall prevention scientists to conceptualize optimal resistance and balance training programs for fall prevention in older adults. The professional knowledge of the expert panel, the framework of the Manual for Falls Prevention Classification System from the Prevention of Falls Network Europe (ProFaNE) and recent state-of-the-art research, especially in a Swiss context, built the basis for the production of a cost-free practice guide open to the public (available in German or French: http://www.stuerze.bfu.ch) [12,47,49].

The proposed trial presented in this article will investigate the effects of a fall prevention exercise program developed by an expert panel on intrinsic fall risk factors (i.e., balance, strength / power), body composition, cognitive function, psychosocial well-being, and falls-self efficacy. The applied research tools will allow diagnosis of sarcopenia according to the EWGSOP guidelines. Thus, we will be able to evaluate prevalence of sarcopenia in our participants, and conduct sensitivity and specificity analysis for the strength / power assessments including their cut-offs. To facilitate transfer into clinical practice, simple clinical tests for each instrumented test will be provided to alleviate fall risk assessment and exercise prescription adjustment. In addition to an easy implementation into practice, this will allow cross-validation of the applied research instruments (clinical vs. instrumented). Further, this work may help to promote the protocol of the expert panel and the rationale behind the practice guide to people with English as their native language. We hypothesize that our training program will positively influence balance, strength / power, body composition as well as cognition, psychosocial well-being, and falls-self efficacy in older community-dwelling people.

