## Methods/Design

### Participants

Community-dwelling older adults aged 65 to 80 years without neurophysiologic diseases will be included in this single centre, randomised, controlled study. Figure 1 shows a flow chart of the study design. Eligibility will be screened with the Standard Assessment Protocol of the Acute Geriatrics Department at the University Hospital Basel / Felix Platter-Hospital Basel including demographic, anthropometric and medical data to rule out contraindications to exercise. Participants will be excluded when they reach cut-off scores for the following tests: Mini Mental State Examination score (MMSE, <24 points) [50,51], Clock Drawing Test (CDT, pathological test performance) [52], Tuning Fork test (individual vibration threshold) [53], Falls Efficacy Scale – International (FES-I, >24 points) [54], World Health Organisation Quality of Life Assessment-Bref (WHOQOL-Bref) [55], and the Freiburg Questionnaire of Physical Activity (FQoPA, less than 1 hour of everyday and sports-related physical activity per week) [56]. Evidence showed that even sedentary older adults are not at increased risk for injury when performing an exercise program compared to young adults [57]. Written informed consent will be obtained from all older adults prior to inclusion. This study is approved by the ethics committee of the University of Potsdam (reference number 34/2012), Germany, and will be conducted according to the ethical standards of the Helsinki Declaration.

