The current trial will add valuable information to the knowledge of dose–response-relations for exercise in older adults. Particularly the use of two different intervention arms (extensive supervised group exercise program vs. short home-based exercise program) will give some indication of the minimal amount of exercise needed to stimulate physical performance adaptations. If the short version of the program (3 times per week for 30 min.) will prove to be effective, this may lower the barrier for sedentary older adults to take up exercising. If intrinsic fall risk factors can be positively influenced by our proposed intervention regime, future trials will need to investigate any possible effect on fall rate in older adults. Additionally, in this trial, each clinical test will be compared to a gold-standard instrumented test. This cross-validation may facilitate the implementation of easy-to-administer balance and strength / power assessments into practice. Regular simple balance and strength / power assessments are important for training prescription and performance regarding exercise variation and progression. Furthermore, measuring gait velocity, grip strength and muscle mass will allow diagnosis of sarcopenia according to EWGSOP criteria, and may add knowledge to sensitivity and specificity of strength / power test to this important geriatric syndrome.

In summary, this trial will provide insight into the effect of fall prevention exercise applicable for a broad population and setting, both in community and sporting groups and at home. Practitioners, exercise therapists, and instructors will be provided with a feasible, validated exercise routine whose effect on intrinsic fall risk factors is scientifically evaluated. Furthermore, older adults who participate in the present program represent possible multipliers for a broader acceptance of important exercise and health-enhancing measures. Finally, the results of the current trial may help to further develop theories and models explaining balance and resistance training effects in general and particularly in older adults.

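### Handgrip would be scored against a sarcopenia diagnosis that it helps define, and 54 healthy participants can give only imprecise sensitivity for the other three strength / power tests

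*Protocol article*

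**What the plan says.** The Background announces that the trial will be able to "conduct sensitivity and specificity analysis for the strength / power assessments including their cut-offs". The Discussion makes the target condition clear: the measurements "may add knowledge to sensitivity and specificity of strength / power test to this important geriatric syndrome", meaning sarcopenia.

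The index tests are listed in the Abstract (Methods/Design) as "strength (i.e., hand grip strength test; Chair Stand Test), and power (i.e., Stair Climb Power Test; countermovement jump". The section on strength / power assessment describes the same four, with handgrip first.

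The reference diagnosis is described in the Background as "low muscle mass plus either low muscle strength or low physical performance measured by gait velocity (≤80 cm/s), grip strength and muscle mass". The Discussion confirms how it will be formed in this trial: "measuring gait velocity, grip strength and muscle mass will allow diagnosis of sarcopenia according to EWGSOP criteria".

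On the sample, the Abstract states "Healthy old people (n = 54) between the age of 65 to 80 years will participate in this trial". The Participants section adds "Community-dwelling older adults aged 65 to 80 years without neurophysiologic diseases will be included" and excludes, among others, people reporting "less than 1 hour of everyday and sports-related physical activity per week". The section on statistics and sample size bases the 18 per arm on an earlier study of balance training and postural control. That section covers repeated measures ANOVA, post-hoc tests and correlations.

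**The concern.** Grip strength appears on both sides of the planned comparison. It is a test whose accuracy is to be estimated, and it is one of the measurements that decide who counts as a case. This is incorporation bias: agreement between test and reference is raised by construction, whatever the test contributes on its own. Nothing in the article takes handgrip out of the index tests.

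The remaining tests face a problem of numbers. A sample of 54 healthy people, sized for a training effect, may contain few people with sarcopenia, and sensitivity is estimated from those people alone.

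The article wants simple tests to move into practice. An inflated accuracy figure for handgrip, or a cut-off tuned to a few cases, could be taken up as if it were established.

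**Working it through.** **1. The plan's own figure.** Three arms of 18 give 3 × 18 = 54, which matches the Abstract. The 10% dropout step is consistent with 16 evaluable per arm: 16 / 0.90 = 17.8, rounded up to 18. The article gives no figure for sarcopenia prevalence, case numbers or precision of sensitivity, so there is nothing of that kind to reproduce.

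**2. Which tests overlap with the reference.**

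| Measurement | Index test in this analysis | Part of the reference |
|---|---|---|
| Handgrip | yes | yes |
| Chair Stand | yes | no |
| Stair Climb Power | yes | no |
| Countermovement jump | yes | no |
| Gait velocity | no | yes |
| Muscle mass | no | yes |

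One test of four is on both sides.

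**3. How much incorporation can do.** The reference is positive when muscle mass is low and either grip is low or gait is slow. Let m, a and b be the probabilities of low muscle mass, low grip and slow gait. As an illustration, suppose the three are independent, so that low grip says nothing about muscle mass. With the same grip cut-off for test and reference:

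- sensitivity of low grip = a / (a + b − ab)
- specificity of low grip = 1 − a(1 − m) / [1 − m(a + b − ab)]

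Assume a = 10% and m = 20% (neither is in the documents). Against low muscle mass alone, the sensitivity of grip would be just a = 10%. Against the combined definition it becomes:

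| Assumed slow gait b | a + b − ab | Apparent sensitivity | Apparent specificity |
|---|---|---|---|
| 1% | 0.109 | 92% | 92% |
| 2% | 0.118 | 85% | 92% |
| 5% | 0.145 | 69% | 92% |
| 10% | 0.190 | 53% | 92% |

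The effect shrinks as more cases qualify through slow gait, and at b = 20% the sensitivity is 36%. It is large when slow gait is rare.

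**4. Precision for the other three tests.** Expected cases = 54 × prevalence, with prevalence assumed. If all c cases are detected, the exact (Clopper-Pearson) lower 95% limit is 0.025^(1/c).

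| Assumed prevalence | Expected cases | 95% range of cases | All detected | Close to 80% detected |
|---|---|---|---|---|
| 5% | 2.7, about 3 | 0 to 6 | 3/3: 29-100% | 2/3: 9-99% |
| 10% | 5.4, about 5 | 2 to 10 | 5/5: 48-100% | 4/5: 28-99% |
| 20% | 10.8, about 11 | 5 to 17 | 11/11: 72-100% | 9/11: 48-98% |

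As a benchmark, a half-width of 10 percentage points at a true sensitivity of 80% needs 1.96² × 0.8 × 0.2 / 0.1² = 61.5, so 62 cases. That exceeds the 54 participants, so it is out of reach at any prevalence. Specificity fares better because most participants are non-cases: 41 of 51 gives 67-90%.

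**The case against.** Several points can fairly be made for the plan.

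- *The aim is ancillary.* It is worded as something the trial will make possible. It is outside the stated hypothesis, the primary outcomes and the sample-size basis, and it cannot bias the comparison of the three arms. This stands, and it sets the weight of the point.
- *An analysis plan that is not shown may restrict the index tests.* This is possible. The published text nevertheless covers the strength / power assessments without exception, and followed as written it includes handgrip.
- *The case numbers are assumed.* This stands. The documents give no prevalence, and estimating it is one of the trial's aims. The activity criterion is a low bar, since it excludes only people below one hour a week with everyday activity counted. At 20% prevalence about 11 cases would be expected, and the interval is still wide.

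Some stronger readings are tempting but are not supported:

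- A reader might infer that the whole analysis is circular. Three of the four tests do not enter the reference.
- A reader might infer that handgrip sensitivity must be 100%. That holds only for cases reached through low strength. Someone with low muscle mass and slow gait but normal grip is a case that handgrip misses, and someone with low grip but normal muscle mass is a false positive.
- A reader might extend the criticism to gait velocity. The article assesses it under balance and gait and uses it in the reference, but never proposes it as an index test for sarcopenia.
- A reader might infer that new cut-offs will be derived. The mention of cut-offs can equally mean existing ones, and the article already gives published performance bands for the Chair Stand Test.

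**Conclusion.** The point holds in a limited form. Handgrip is an index test and also part of the reference, so its accuracy would be partly inflated by construction. This follows from the text and needs no outside figure. The size of the inflation does rest on assumptions: under independence, with 10% low grip and 1% to 10% slow gait, a grip test unrelated to muscle mass would show a sensitivity of 53% to 92%.

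For Chair Stand, Stair Climb Power and countermovement jump there is no circularity, only imprecision. At assumed prevalences of 5% to 20%, the lower exact 95% limit for sensitivity lies between 29% and 72% even when no case is missed.

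The point is minor. It concerns how much an ancillary analysis can claim, and it has no bearing on the treatment comparisons.

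**What to change.** Limit the index tests for sarcopenia to Chair Stand, Stair Climb Power and countermovement jump, and state that handgrip is excluded because it enters the reference diagnosis. Say that only existing cut-offs will be evaluated and that none will be derived from this sample. Label the analysis exploratory, and report the number of cases with exact 95% intervals beside each estimate.

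The change is one of wording and needs no new data or participants. The cost is a smaller claim: the trial would no longer offer an accuracy figure for handgrip, and what it adds about the other tests for sarcopenia would be descriptive.
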